## Abstract

**Background::**

Hepatitis B virus (HBV) infection is an important public health problem in the Turkish population, that is, one of the largest migrant populations in Europe. With the introduction of cost-effective antiviral treatments in the past decade, there is a need to identify HBV-infected patients who may benefit from treatment. This study describes the design of a study to assess the HBV prevalence in the Turkish population living in Belgium. Additionally, we will determine the risk factors of HBV infection and the uptake of screening, vaccination, and antiviral treatment in this hard-to-reach Turkish population.

**Methods::**

A longitudinal, epidemiological study will be conducted in the region Middle Limburg Belgium, where the Turkish adult population, 18 years of age and older, will be screened for hepatitis B surface antigen (HBsAg), antibodies against HBsAg (anti-HBs), and antibodies against hepatitis B core antigen (anti-HBc). Educational meetings concerning viral hepatitis B will be organized and there will be 3 ways to be screened for HBV: immediately after the educational meetings, at the Outpatient Hepatology Department of Ziekenhuis Oost-Limburg, and at home visits. Subsequently, participants will be asked to fill in a questionnaire regarding sociodemographic factors, migration history, risk factors for HBV infection (e.g., sharing toothbrushes, HBV-infected family member), and HBV vaccination status. Six months after screening, HBsAg-positive patients will be assessed whether they are under follow-up at the general practitioner or hepatologist. We will also gather information regarding the uptake of vaccination in nonimmunized subjects.

**Discussion::**

This study will provide information about the HBV prevalence and distribution of the stages of liver disease in the Turkish population in Belgium. By determining the risk factors for HBV infection, subgroups with an increased prevalence of HBV infection can be identified.

**Clinical trial number::**

This clinical trial is registered at clinicaltrials.gov (NCT03396458).

## Introduction

1

Hepatitis B virus (HBV) infection is an important public health problem. In the year 2017, approximately 257 million people are chronically infected worldwide and at risk of developing serious sequelae, such as cirrhosis and hepatocellular carcinoma.^[1,2]^

According to the WHO, Turkey is one of the countries with intermediate endemicity for hepatitis B. The hepatitis B surface antigen (HBsAg) prevalence thereby changes from 2% to 3% in the Western part of the country to 7% to 8% in Eastern part.^[3]^ In intermediate endemic countries, such as Turkey, horizontal HBV transmission by nonsexual close contact besides perinatal, sexual, and parenteral transmission is the main route of infection.^[4–7]^ Risk factors associated with horizontal transmission in childhood are poor socioeconomic conditions, the presence of a HBsAg-positive family member and the habit of sharing various personal and household articles within the home (e.g., contaminated toothbrush, contaminated towels).^[5,8,9]^

In contrast, the HBsAg prevalence is low (<1%) in the general population of Belgium and many other Western European countries.^[10,11]^ Sexual transmission of HBV in persons with high-risk sexual behavior (e.g., men who sex with men, heterosexual persons with multiple sex partners) remains a common source of HBV transmission in these low endemic countries.^[2]^

Starting in 1961, political, economic, and social developments led Turkish people to migrate to Europe, Australia, Arab countries, and former Soviet Union countries.^[12]^ According to Turkish government statistics, 5.5 million Turkish citizens live abroad, of whom around 4.6 million live in Western European countries.^[13]^ Turkish citizens are therefore one of the largest migrant groups in Europe. Moreover, a recent study by Ahmad et al^[14]^ indicated that the Turkish population was ranked 3rd as migrant group with the highest absolute number of chronic HBV cases in Europe. However, their estimates of HBsAg prevalence were based on prevalence studies conducted in Turkey. Another study conducted by a Dutch group showed that the Turkish population in the Netherlands had a low level of awareness and knowledge regarding HBV infection which could subsequently impinge the attitude toward HBV screening.^[15]^

Nonetheless, little is known about the true prevalence and risk factors of HBV infection among the Turkish population living in Western European countries. Considering the fact that infection with HBV in children most often result in chronic infection^[16]^ and universal HBV vaccination in Belgium and Turkey only started after, respectively, 1999^[17]^ and 1998^[3]^, an appreciable number of the Turkish population in Belgium may be infected with HBV. Many of the HBV-infected Turkish patients may also remain undiagnosed, since the onset of HBV and progression to cirrhosis and hepatocellular carcinoma is generally asymptomatic and occur many years after exposure.^[18]^ As HBV treatment options have greatly improved over the past decades and have proven to be cost-effective, there is a need to identify chronic carriers who may benefit from treatment.^[19–21]^ Therefore, this study aims to assess the prevalence and risk factors of HBV infection in hard-to-reach Turkish population living in Belgium. The identification and early antiviral treatment of HBV infection in the Turkish population could prevent the development of end-stage liver disease and further spread, while the associated health cost burden in this group at risk can be reduced.

## Methods/design

2

### Study design

2.1

The current study is a longitudinal, epidemiological study.

### Study population

2.2

The study population consists of Turkish individuals, living in the region Middle Limburg in Belgium.

Inclusion criteria:

Eighteen years and older of ageTurkish individuals (defined as persons who are born in Turkey or persons of whom one of the parents is born in Turkey)All participants irrespective of being aware of having been tested and knowing their HBV statusAll participants irrespective of being aware of having been fully vaccinatedSigned informed consent form

Minors, incapacitated subjects, and non-Turkish individuals were to be excluded from the study.

### Pre-screening phase

2.3

In the pre-screening phase, we developed a brochure, flyer, poster, and video focusing on HBV infection. The patient information and consent form, questionnaire, brochure, flyer, poster, and video were translated in the Turkish language by a certified translator. The final information in Dutch and Turkish language were then thoroughly checked by delegates of Turkish associations and the questionnaire was pilot tested by 10 persons of Turkish origin, first and 2nd-generation migrants, males and females, from different age categories (age group 18–39 years, 40–59, 60–79, and 80+).

During the study, participants will be able to contact the first author by phone or e-mail for Turkish/Dutch information and questions. This study will be communicated to the association of general practitioners (GPs) in Genk, a city in the region Middle Limburg, who will be kept well-informed throughout the study.

### Recruitment

2.4

An estimated 17,510 Turkish persons live in the region Middle Limburg, of whom approximately 11,540 are 18 years of age and older (Limburg in cijfers, personal communication). Before the start of the screening phase, focus group discussions were held with delegates of 4 mosques in Middle Limburg (Waterschei, Winterslag, Kolderbos and Sledderlo) and 2 Turkish responsibles of the Genk city council. Group discussions included general information on hepatitis B (e.g., hepatitis B occurs more often in Turkey compared to Belgium, routes of transmission, asymptomatic nature of disease, disease outcome), prevention (e.g., screening, vaccination), design of this study, recruitment, and conduct of the study. Being familiar with the stigma regarding hepatitis in the Turkish community, several motivating factors and barriers to go for HBV screening were identified during the group discussions. Tables 1 and 2 illustrate the motivating factors and barriers by social-cultural, religious, and other factors as well as the appropriate actions in the current screening study.

**Table 1 T1:**
[figure not shown]
Motivating factors for hepatitis B virus screening identified during focus group discussions and actions taken in current study.

**Table 2 T2:**
[figure not shown]
Barriers for hepatitis B virus screening identified during focus group discussions and actions taken in current study.

As the Islamic mosques mainly consist of male members/visitors, we will also search for female Turkish organizations in the Middle Limburg area. From September 2017 until August 2019, with the support of key figures within these organizations, we will organize educational meetings with the possibility for immediate HBV screening afterwards. The educational and screening sessions will be scheduled after the regular meetings of each organization.

The key figures within these organizations will distribute invitations for the sessions using information flyers, posters, and name cards with a link to the hepatitis B video. The flyers, posters, and video contain information about risk factors for horizontal transmission (sharing personal and household articles, such as toothbrushes) and vertical transmission in addition to general information such as HBV vaccination, consequences of unrecognized HBV, and the possibility of antiviral treatment. Turkish persons who are unable to attend a session will be invited to visit additional educational meetings and screening sessions in Ziekenhuis Oost-Limburg (ZOL) or can make an appointment with [name] at the Hepatology Outpatient Department (OPD) of ZOL. In addition to the abovementioned methods, Turkish people can also contact the first author for home visits with the possibility to sign an informed consent and be screened for HBV. Figure 1 shows the flowchart of the study design.

**Figure 1 F1:**
[figure not shown]
Flowchart of the study design. HBV = hepatitis B virus, HBsAg = hepatitis B surface antigen, anti-HBs = antibodies against hepatitis B surface antigen, anti-HBc = antibodies against hepatitis B core antigen, ZOL = Ziekenhuis Oost-Limburg.

### Screening phase

2.5

The educational sessions will be held in Turkish by the first author who will address the risk factors, routes of transmission, the fact that screening is free of charge, consequences, prevention, and HBV treatment. After the educational meetings, there will be the possibility to be screened for HBV. Those who opt for screening will be given an informed consent form and a questionnaire, available in Dutch and Turkish. HBV screening will also be possible at home visits and at the OPD of ZOL. Blood specimens will be transported to and processed in the laboratory of ZOL.

### Laboratory testing

2.6

All blood samples will be tested for HBsAg, antibodies against HBsAg (anti-HBs), and antibodies against hepatitis B core antigen (anti-HBc) using an electrochemiluminescence assay (Cobas 8000 e602, Roche, Germany). The interpretation of positive and negative results will be carried out as recommended by the test producer.

### Post-screening phase and follow-up actions

2.7

Patients who test positive for HBsAg will have the opportunity to enter an OPD. HBV screening results will be sent by letter to the patients and to their GP. A clinical work-up and treatment program in the OPD will be proposed for newly diagnosed patients. No further action will be undertaken in previously registered HBsAg-positive patients.

Nonimmunized subjects and their GP will be informed about the test results by a letter. Nonimmunized subjects will additionally be asked to consult their GP for HBV vaccination. In case of immunization against HBV infection, only a letter regarding the HBV screening results will be sent to the participant as well as to the GP.

### Sample size

2.8

Sample size calculation was performed with the aid of Epi Info (version 7.2, Centers for Disease Control and Prevention [CDC], Atlanta, GA). Considering the lack of data on the number of first and second-generation Turkish migrants living in Middle Limburg, the number of samples per age was calculated instead so that the results of the sample group agree with that of the Turkish population in Middle Limburg with a confidence interval of 95% and 3% as an acceptable margin of error. The expected frequencies for the different age categories 18 to 39, 40 to 59, 60 to 79, and 80+ are 54%, 35%, 9%, and 1%, respectively (Limburg in cijfers, personal communication). Our analysis would lead to a total of 1000 tested persons.

### Measures

2.9

Questionnaire: we searched PubMed to identify articles on risk factors for HBV infection in the Turkish community using the following terms and keywords alone and/or in appropriate combinations: hepatitis B, Turkey, Turkish, Turks, risk factor. No publication date or language restrictions were set. In addition, reference lists of all identified articles were checked to identify additional material, including (grey) literature. The final questionnaire includes the following risk factors: blood transfusion (no, yes before 1974 in Turkey, yes before 1974 in Belgium, other), dental treatment (yes in Turkey, other), (if female) gynecological examination (no, yes in Turkey, yes in Belgium, other), (if male) circumcision (no/yes), (if male) circumcision carried out by a doctor (no, yes, unknown), (if male) way of circumcision (alone, collective, unknown), surgery (no, yes in Turkey, yes in Belgium, other), treatment with needles (no, yes in Turkey, yes in Belgium, other), HBV-infected mother (no/yes), HBV-infected father (no/yes), HBV-infected brother (no/yes), HBV-infected sister (no/yes), HBV-infected partner (no/yes), other infected family member (no/yes), sharing toothbrushes with other household members (no, yes once, yes on regular basis), sharing nail clippers with other household members (no/yes), sharing razors with other household members (no/yes), sharing used towels with other household members (no/yes), eating from the same plate as other household members (no/yes), tattoo/piercing/earlobe perforation (no, yes in Turkey, yes in Belgium, other), treatment with Fish spa (no, yes in Turkey, yes in another country than Turkey). Furthermore, the questionnaire will collect data on HBV vaccination (vaccinated no/yes/unknown), (if yes) number of vaccinations, (if no) reasons of not being vaccinated) and previous HBV test results. Data regarding sociodemographics (age, gender, educational status of mother, educational status of father), first language (Dutch/Turkish), migration history (country of birth, (if born in Turkey) year of migration to Belgium, mother's country of birth, father's country of birth, (if mother born in Turkey) region of birth from mother, (if father born in Turkey) region of birth from father) will be collected to characterize the study population. Regarding region of birth, Turkey will be divided in the 7 geographical regions: Marmara, Aegean, Mediterranean, Central Anatolia, Black Sea, Eastern Anatolia, and Southeastern Anatolia (Fig. 2).^[3]^ The questionnaire will not cover questions regarding intravenous drug use or sexual behavior as these questions could lead to a significant lower participation rate and the answers to these questions are not reliable in this Turkish population with a majority being Muslim.

**Figure 2 F2:**
[figure not shown]
Map of Turkey according to the geographical regions. Map of Turkey according to regions: (A) Marmara, (B) Aegean, (C) Mediterranean, (D) Central Anatolia, (E) Black Sea, (F) Eastern Anatolia, and (G) Southeastern Anatolia.

Clinical outcomes: within 6 months of a HBsAg-positive test result, we will assess whether or not HBsAg-positive patients are under follow-up at the GP or hepatologist. Clinical follow-up data will be collected: coinfection (hepatitis C virus, hepatitis delta virus, HIV); determination of liver disease stage (via fibroscan, ultrasonography abdomen, magnetic resonance imaging of the liver, duodenoscopy, and, if necessary, liver biopsy); and treatment eligibility, initiation and outcomes. Outcomes of Fibroscan and/or liver biopsy will be scored according to the METAVIR classification system for fibrosis (F0: no fibrosis, F1: portal fibrosis without septa, F2: few septa, F3: numerous septa without cirrhosis, F4: cirrhosis).^[22]^ Within 6 months after HBV screening, we will also gather data regarding nonimmunized subjects, namely, if they initiated HBV vaccination by the GP.

### Primary outcome measure

2.10

The primary outcome variable is the prevalence of current infection with HBV in the Turkish population living in Middle Limburg. For this reason, one Li-heparin tube collection and subsequent HBsAg analysis will be performed from each participant.

### Secondary/exploratory outcome measures

2.11

The questionnaire will provide information on secondary outcomes by assessing the risk factors for recent or past HBV infection (anti-HBc positivity). We will also determine the willingness for HBV assessment in the Turkish population in Middle Limburg. This will be assessed by the number of persons who did go for HBV testing divided by the total population who attended one of the educational meetings, the OPD of ZOL or home visit. Other secondary outcome measures are percentage of new HBsAg-positive patients that are under follow-up at the GP or a hepatologist, factors associated with HBsAg-positive persons to be under follow-up at the GP/hepatologist 6 months after HBV screening test result, distribution of stages of liver disease in HBsAg-positive patients, treatment eligibility, initiation, and outcomes in HBsAg-positive patients, the percentage of Turkish population who are immune against HBV infection based on anti-HBs status, and percentage of Turkish population who are susceptible for HBV infection, and uptake of HBV vaccination in nonimmunized Turkish subjects.

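### The willingness outcome measures uptake among people who came forward, pooled over routes of differing selection, and so cannot be read as willingness in the Turkish population of Middle Limburg

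*Protocol article*

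**What the plan says.** Section 2.11 (Secondary/exploratory outcome measures) states the target: "We will also determine the willingness for HBV assessment in the Turkish population in Middle Limburg". The definition follows at once. Its numerator is everyone who was tested, by whatever route; its denominator is fixed by the words "divided by the total population who attended one of the educational meetings, the OPD of ZOL or home visit". All three routes therefore enter one numerator and one denominator.

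The routes are described elsewhere in the protocol article:

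- **Meetings.** Under section 2.4 (Recruitment) these are scheduled to follow the host organisation's regular meetings. Section 2.5 (Screening phase) makes testing optional: "After the educational meetings, there will be the possibility to be screened for HBV".
- **Hospital (ZOL).** Section 2.4 offers people who cannot come to a session either further educational meetings with screening at the hospital or an individual appointment in the outpatient department (OPD).
- **Home.** Also in section 2.4: "Turkish people can also contact the first author for home visits with the possibility to sign an informed consent and be screened for HBV".

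The Methods part of the abstract lists the OPD and home visits, beside the meetings, as ways of being screened. On data collection, section 2.5 says: "Those who opt for screening will be given an informed consent form and a questionnaire". Section 2.4 gives the size of the regional Turkish population, "of whom approximately 11,540 are 18 years of age and older".

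**The concern.** Two features of the definition do not fit the stated target.

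First, the target is a population, but the denominator holds only people who turned up. An adult who saw a flyer or was invited by a key figure and stayed away counts nowhere. Section 2.4 itself describes stigma and barriers to screening in this community, so those who stay away plausibly include the less willing.

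Second, the people in the denominator were selected in different ways. A meeting attendee meets the offer of a test after an educational talk, and accepting or declining is informative. Someone who books an OPD appointment or asks for a home visit has mostly decided already. Such people add nearly as much to the numerator as to the denominator, which pulls the ratio towards 1. The reported percentage then depends partly on how many home visits and appointments took place, not only on how people responded to the offer.

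At stake is what can be concluded about acceptability. Section 3.1 says the study will inform on feasibility and acceptability of screening in hard-to-reach migrant groups. It does not name this ratio as the basis, but a reader would naturally turn to it. The limitations in section 3.1 do not mention this selection.

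**Working it through.** The document states no willingness figure, so there is nothing to reproduce. The check asks how the pooled ratio behaves.

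**Inputs from the document**

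- Planned number tested: 1000 (section 2.8).
- Adults in the target population: about 11,540 (section 2.4).

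**Assumed inputs (none is in the document)**

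- *u*, uptake among meeting attendees: 0.3 to 0.9.
- *q*, uptake among OPD-appointment and home-visit contacts: 1.0 or 0.9.
- *s*, share of tested persons who came by OPD appointment or home visit: 0.1 to 0.4.

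**Formula.** With 1000 tested, meetings contribute 1000(1 − s)/u people to the denominator and the other two routes contribute 1000s/q. Hence

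pooled ratio = 1000 / [1000(1 − s)/u + 1000s/q] = 1 / [(1 − s)/u + s/q].

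For s > 0 this exceeds u exactly when q > u, and equals u when q = u.

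**Worked case.** Take u = 0.5 and q = 1.

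- s = 0.1: 1000 / (1800 + 100) = 1000/1900 = 0.526.
- s = 0.2: 1000 / (1600 + 200) = 1000/1800 = 0.556.
- s = 0.4: 1000 / (1200 + 400) = 1000/1600 = 0.625.

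**Range**

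| Meeting uptake u | q | s = 0.1 | s = 0.2 | s = 0.4 |
|---|---|---|---|---|
| 0.3 | 1.0 | 0.323 | 0.349 | 0.417 |
| 0.5 | 1.0 | 0.526 | 0.556 | 0.625 |
| 0.5 | 0.9 | 0.523 | 0.549 | 0.608 |
| 0.7 | 1.0 | 0.722 | 0.745 | 0.795 |
| 0.9 | 1.0 | 0.909 | 0.918 | 0.938 |
| 0.9 | 0.9 | 0.900 | 0.900 | 0.900 |

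At q = 1 the excess over meeting uptake is about 2 to 12 points for u = 0.3, 3 to 13 points for u = 0.5, and 1 to 4 points for u = 0.9. It is zero when uptake is equal across routes. With u held at 0.5 and q at 1, moving s from 0.1 to 0.4 changes the result by 0.625 − 0.526 = 0.099, about 10 points, although uptake on each route is unchanged.

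**Can the planned weighting repair this?** No. Section 2.12 bases its age and gender weights on samples linked to questionnaires, and section 2.5 gives the questionnaire only to those who opt for screening. People who decline and people who never attend cannot be weighted in.

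**Reach.** 1000/11,540 = 0.087, or 8.7% of adults in the region at the planned number tested.

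**The case against.** The other side has several good points.

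- **The denominator is openly stated**, so a careful reader can see that it is uptake among attendees. This stands as mitigation, but the sentence before it still names a different quantity.
- **Uptake on the OPD and home routes may not be complete.** A reader might infer that everyone on these routes is tested by construction. The documents do not support that: sections 2.4 and 2.5 speak of screening being possible there, so a person may decline. Part of the hospital route consists of further educational meetings, which resemble the meeting route at another site. This stands: the upward shift is likely, not certain.
- **Double counting is not in the text.** A reader might infer that someone who attends a meeting and is later tested at the OPD or at home enters the denominator twice. Section 2.11 counts persons, and its denominator is a population joined by *or*, which reads as unique people. Double counting would in any case lower the ratio.
- **Every tested person is in both numerator and denominator of any proportion.** True, and that is not the fault. The fault is that entry by two of the routes depends on willingness.
- **Reach is not willingness.** A reader might set 8.7% against the pooled percentage as the true figure. It follows from the planned number tested and says nothing about how people not reached would respond.
- **Meeting attendees are self-selected too.** This stands, so restricting the ratio to meetings cures the pooling but not the label.
- **An article may leave a breakdown by route to the full plan.** Fair, but the definition is given here explicitly, and it is the definition that misses its target.

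**Conclusion.** The point holds in a limited form. The ratio in section 2.11 is uptake among people who came forward and cannot deliver willingness in the Turkish population of Middle Limburg. That mismatch follows from the text alone and needs no assumption.

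The upward shift from pooling is conditional: it requires uptake at OPD appointments and home visits to exceed uptake at meetings. The way those routes are entered makes this likely. Its size cannot be obtained from the document. The 53% to 63% illustration against 50% meeting uptake rests wholly on assumed inputs, and the shift would be small if meeting uptake were already high.

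A reader might infer that the study's main result is compromised. The documents do not support this: the definition does not enter the primary HBsAg prevalence, the sample size or the risk-factor model. As this is one of several secondary outcomes, the weight is moderate or minor.

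**What to change.** Amend section 2.11 as follows.

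1. Define uptake as meeting attendees tested divided by eligible adult meeting attendees, counting educational meetings held at the hospital as meetings.
2. Report OPD-appointment and home-visit contacts, and the tests done there, as separate counts outside that percentage.
3. Call the measure uptake among attendees, and drop the wording that refers it to the Turkish population.
4. Optionally, show the number tested over about 11,540 adults, labelled as reach.

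The cost is small: some rewording and a count of eligible adults at each meeting, and the present denominator already needs attendance counts. There are two downsides. The reported percentage will probably be less favourable. And because only those who opt for screening receive a consent form and questionnaire, a head count may not identify people who attend more than once and decline, so the meeting denominator may hold some repeat attenders. The report should say so.
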